##### Widespread hyperalgesia

Widespread hyperalgesia indicates facilitated central pain mechanisms.^72^ PPT and CPM measurements will be used to estimate widespread hyperalgesia.

*PPTs* at both symptomatic (bilateral suboccipital muscles) and distant pain-free (bilateral tibialis anterior muscles) areas will be used to determine widespread hyperalgesia. PPTs lower than the 95% CI lower border bound of the normative PPTs will be considered decreased (=deviating).^17^ PPTs at the suboccipitals will not be repeated since data are already collected within the context of CPM (see the Conditioned pain modulation section). PPTs of the bilateral tibialis anterior muscle will be determined as described above (see the Test stimulus: mechanical PPTs and tolerance section). The test order will be standardised as: left tibialis anterior—right tibialis anterior muscle. This procedure will be repeated two times, and measurements per site will be averaged. Averages of the extracted parameters will be used for further analysis.^60^ An extrasegmental *CPM measurement* will be performed as second proxy to estimate widespread hyperalgesia (online supplemental figure S2).

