#### Profiling-related outcome—pain profile

Participants will be categorised in four pain profiles based on responses to the TSP and CPM (figures 1–3):

P-P I: pronociceptive (increased TSP/impaired CPM).

P-P II: pronociceptive (normal TSP/impaired CPM).

P-P III: pronociceptive (increased TSP/normal CPM).

P-P IV: antinociceptive (normal TSP/normal CPM).

Each participant with CeH will be categorised into a pain profile per measurement location (TSP at the hand and face, CPM at the left and right suboccipital muscles).^49 50^ Additional presence of widespread pain will be evaluated (figure 4). The paragraphs below contain information on the definitions of increased/decreased TSP, impaired/normal CPM and presence of widespread hyperalgesia.

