### Statistics

Primary analyses will report results relating to outcomes on feasibility. Descriptive statistics and content analysis will be used to assess feasibility of the protocol. The feasibility study will provide useful information with regard to planning, testing study procedures (eg, estimation of the recruitment rate, plausibility of multicentre collaborations, etc), and investigating outcomes to support adequate sample size calculation.^73^ Data from the CMP and TSP measurements will be used to estimate post hoc sample size (G*Power V.3.1.9.4, Kiel Germany) for a larger trial.

Individual PMPs of at least 12 participants with CeH will be mapped based on the methods outlined in the Profiling-related outcome—psychosocial lifestyle profile and conditioned pain modulation sections. Secondary analyses will involve an analysis of proportions (%) of the different psychosocial lifestyle profiles and pain profiles. Currently no data are available in people with CeH, therefore a pragmatic approach is proposed based on the work of Julious who recommended 12 participants as the minimum for pilot studies.^74^ Justifications for this sample size are based on rationale about feasibility and precision about the mean and variance.^74^ Both primary and secondary analyses will be used to decide whether the feasibility study should be expanded to a full-scale study. The latter implies registering of the trial in accordance with the WHO Trial Registration Data Set (V.1.3.1).

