## Discussion

### Relevance of the study

‘Maybe not all therapeutic interventions are appropriate for all people with CeH’.^12^ With this statement, Fernández-de-Las-Peñas *et al* drew attention to an important problem in the management of CeH. Others have hypothesised that not all people with CeH can be managed successfully by only targeting the upper cervical spine.^12 13 15^ Chua *et al* advised that the management of CeH should not exclusively focus not only on the cervical nociceptive source but also on central nervous system sensitisation spreading to the level of the trigeminal spinal nucleus.^75^

Findings of previous work of our group confirmed this by identifying secondary and tertiary hyperalgesia (ie, increased pain sensitivity in undamaged tissue away from, and contralateral of the nociceptive source). Meaning that both bilateral cephalic and extracephalic PPTs were lower in people with CeH compared with healthy asymptomatic controls.^17^ However, these findings do not imply that peripheral nociceptive sources should be ignored. Such sources could initiate, maintain and modulate facilitated central pain processes. Therefore, potential nociceptive sources alongside psychological, behavioural and social components should also be assessed (ie, interplay of bottom-up and top-down mechanisms).^76^

Although CPM testing was already applied to people experiencing various types of headache such as chronic migraine, tension-type headache and post-traumatic headache,^18 77–79^ it was only once administered to people with chronic CeH.^75^ These people with chronic CeH experienced moderate pain (numeric pain rating scale 6.5±1.8) during CPM testing. We propose to analyse endogenous pain modulation during a headache-free phase. Having a less efficient CPM, when being headache free, suggests that on a pain-generating event, the person is at a higher risk to develop pain than people showing an efficient CPM at baseline.^29^

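### The cut-off for a decreased individual PPT is a 95% confidence bound, which as written limits the normative mean and not the individual, so it over-labels healthy people at each site

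*Protocol article*

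**What the plan says.** Under Widespread hyperalgesia, the protocol article compares each participant's PPTs with norms from its reference 17: "PPTs lower than the 95% CI lower border bound of the normative PPTs will be considered decreased (=deviating"). The PPTs "at both symptomatic (bilateral suboccipital muscles) and distant pain-free (bilateral tibialis anterior muscles) areas will be used to determine widespread hyperalgesia", so the comparison is made at four sites. The label has a mechanistic meaning: "Widespread hyperalgesia indicates facilitated central pain mechanisms". An extrasegmental CPM measurement is named in the same section as a second proxy.

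Experimental protocol lists widespread hyperalgesia as one of three parameters of the pain profile, beside TSP and CPM. Profiling-related outcome—pain profile builds the four categories P-P I to IV from TSP and CPM only, and then adds: "Additional presence of widespread pain will be evaluated (figure 4"). On sample size, Statistics says: "Individual PMPs of at least 12 participants with CeH will be mapped".

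The article does not define 95% CI as a reference interval, a percentile range or a multiple of the SD. It gives no size, mean or SD for the normative sample.

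**The concern.** A confidence interval answers the question of where the normative mean lies. Judging one person needs a different quantity: the range in which most healthy individuals lie. The two differ by a factor of √n in width. A bound on the mean therefore sits close to the mean, and a larger and better normative sample makes the rule less specific, with the share of healthy people labelled tending to 50%.

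The label is read as a sign of facilitated central pain mechanisms. If a large share of healthy people would also carry it, a participant's label says little about that participant. The sections on study population and statistics describe enrolment of people with CeH only, so no concurrent control group would show the inflation. The error also runs towards what the group expects from its earlier work, as Relevance of the study reports: "Meaning that both bilateral cephalic and extracephalic PPTs were lower in people with CeH compared with healthy asymptomatic controls".

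**Working it through.** The article states no specificity or misclassification rate, so there is no figure of its own to reproduce.

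**Inputs**
- Cut-off: lower bound of the 95% CI, from Widespread hyperalgesia, read as a bound on the normative mean.
- Sites: four, from the same section.
- Participants: at least 12, from Statistics.
- Normative sample size n: not given, so a range is shown.
- Assumption: PPTs in healthy people are roughly normal, with mean m and SD s.

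**Formula.** The cut-off is m − 1.96·s/√n. In SD units it lies 1.96/√n below the mean, so s cancels. The share of healthy people below it is Φ(−1.96/√n). For a lower reference limit, m − 1.96·s, the share is Φ(−1.96) = 2.5% whatever n is.

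| Normative n | Cut-off, SDs below mean | Healthy people labelled at one site | Expected among 12 healthy people |
|---|---|---|---|
| 10 | 0.62 | 26.8% | 3.2 |
| 20 | 0.44 | 33.1% | 4.0 |
| 40 | 0.31 | 37.8% | 4.5 |
| 100 | 0.20 | 42.2% | 5.1 |
| Reference limit | 1.96 | 2.5% | 0.3 |

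The share reaches one third at n = (1.96/0.431)², about 21.

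**Sensitivity to the assumptions**
- With the t quantile in place of 1.96, the shares are 23.7% at n = 10, 32.0% at 20, 37.5% at 40 and 42.1% at 100.
- With right-skewed (lognormal) PPTs and an assumed coefficient of variation of 0.4, they are 24.8%, 36.5%, 43.5% and 49.1%.

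Every variant is at least about nine times the 2.5% of a reference limit.

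**From site to participant.** This step needs a rule for combining sites and the correlation between sites, and the text gives neither. As an illustration only, take a per-site share of 33% and an assumed common correlation of 0.5 to 0.9. Requiring all four sites would label 9% to 22% of healthy people, and accepting any one site would label 45% to 63%. With a reference limit the corresponding ranges are 0.1% to 1.0% and 4.7% to 7.8%. The spread shows why no single participant-level figure can be stated.

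**The case against.** The best defence is that the authors meant a 95% range of individual healthy values and used the wrong term. The text speaks of the bound of the normative PPTs, not of their mean, and cites a source that is not at hand. If so, the percentages above do not arise. But the printed term is still wrong, and anyone following it would apply the wrong cut-off.

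A second defence concerns reach, and it stands. The primary outcome is feasibility, and P-P I to IV rest on TSP and CPM. Statistics bases the sample size of a larger trial on CPM and TSP data and names no proportion with widespread hyperalgesia. PPTs are recorded as continuous values, so labels can be recalculated without loss. Design also says that the analyses of outcomes will be adapted after this study.

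Three stronger readings are tempting, and the document does not support them.
- **Most labels would be false positives.** The calculation concerns healthy people, whereas every participant has CeH. With perfect sensitivity and a false-positive rate f, false labels outnumber true ones only if the true prevalence is below f/(1 + f), which is 0.331/1.331 = 25% at n = 20. The article gives neither prevalence nor sensitivity.
- **More than half of healthy people would be called widespread hyperalgesic.** That requires a rule under which one deviating site of four is enough. The article states no such rule, and its wording can equally be read as needing both regions. Figures 1 and 4 and supplemental figure S2, which may show the combination, are not available, so its absence from the text is not counted as an error. The second proxy would also enter.
- **At least a third would be mislabelled per site.** This holds only for a normative sample of about 20 or more.

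**Conclusion.** The point holds as a defect in a stated rule. Taken as written, the cut-off is a bound on a mean and is used to classify individuals. It would label about 27% to 42% of healthy people at each site for a normative n between 10 and 100, against 2.5% for a lower reference limit. The figures assume roughly normal PPTs and a normative sample in that range; the direction and the order of magnitude survive the t and skewed variants.

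The consequence is confined to the per-site deviating label and the widespread-hyperalgesia component that it feeds. How far it carries to the participant-level label, or what share of labelled participants would be wrongly labelled, cannot be established from the article. It should be fixed, but it does not threaten the study's main purpose.

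**What to change.** Replace the 95% CI lower bound with a lower reference limit for individuals at each site, derived from the normative data already cited. Examples are the 2.5th percentile, or mean − 1.96 SD on a suitable scale. State the size of the normative sample. If a reference interval was meant all along, correct the term.

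When applying the limit, report deviation at the suboccipital sites, which the article itself calls symptomatic, separately from deviation at the distant tibialis anterior sites. A reader can then tell a local finding from a distant one.

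The cost is one recalculation from existing data and a sentence or two of text. The measurements do not change. The downside is that fewer participants will be labelled as deviating.

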### Data management plan

Data concerning feasibility, CPM, TSP and widespread hyperalgesia will be electronically collected (.xlsx). Data gathered from the paper questionnaires (PSQI, DASS-21, HIT-6) will be transferred to excel files (.xlsx). Data will be protected by pseudonymising them, restricting access and access only via the multifactor-authentication (KU Leuven Authenticator app). The principal researcher will complete the pseudonymising process and GDPR (General Data Protection Regulation) questionnaire according to the KU Leuven policy. Storing is foreseen in a folder structure (OneDrive, Microsoft 365 Apps for enterprise) to secure: availability of data, confidentiality and sharing data (https://icts.kuleuven.be/storagewijzer/nl). Finished data (ie, the dataset) will be stored at the KU Leuven Research Data Repository (https://www.kuleuven.be/rdm/en/rdr/rdr). This platform enables archiving (at the end of the project), uploading, describing and sharing research data in a legal and controlled manner. Exclusively the principal researcher and principal investigator will have access to all data, other team members will only obtain restricted access. The latter implies that data are anonymous for these team members.

All data will be kept for 10 years, conform the KU Leuven policy. Supportive arguments to keep personal data for 10 years include: verification of results and future research. Final versions of datasets will be preserved for the long term on internal KU Leuven data storage facilities.

### Statistics

Primary analyses will report results relating to outcomes on feasibility. Descriptive statistics and content analysis will be used to assess feasibility of the protocol. The feasibility study will provide useful information with regard to planning, testing study procedures (eg, estimation of the recruitment rate, plausibility of multicentre collaborations, etc), and investigating outcomes to support adequate sample size calculation.^73^ Data from the CMP and TSP measurements will be used to estimate post hoc sample size (G*Power V.3.1.9.4, Kiel Germany) for a larger trial.

Individual PMPs of at least 12 participants with CeH will be mapped based on the methods outlined in the Profiling-related outcome—psychosocial lifestyle profile and conditioned pain modulation sections. Secondary analyses will involve an analysis of proportions (%) of the different psychosocial lifestyle profiles and pain profiles. Currently no data are available in people with CeH, therefore a pragmatic approach is proposed based on the work of Julious who recommended 12 participants as the minimum for pilot studies.^74^ Justifications for this sample size are based on rationale about feasibility and precision about the mean and variance.^74^ Both primary and secondary analyses will be used to decide whether the feasibility study should be expanded to a full-scale study. The latter implies registering of the trial in accordance with the WHO Trial Registration Data Set (V.1.3.1).

## Ethics and dissemination

All test procedures involving human participants will be in accordance with the ethical standards of the institutional research committees and with the 1964 Helsinki Declaration and its later amendments. Ethical approval was granted by the Ethics Committee Research UZ/KU Leuven (Registration number B3222024001434) on 30 May 2024. Results will be published in peer-reviewed journals, at scientific conferences, and through press releases.

## Discussion

### Relevance of the study

‘Maybe not all therapeutic interventions are appropriate for all people with CeH’.^12^ With this statement, Fernández-de-Las-Peñas *et al* drew attention to an important problem in the management of CeH. Others have hypothesised that not all people with CeH can be managed successfully by only targeting the upper cervical spine.^12 13 15^ Chua *et al* advised that the management of CeH should not exclusively focus not only on the cervical nociceptive source but also on central nervous system sensitisation spreading to the level of the trigeminal spinal nucleus.^75^

Findings of previous work of our group confirmed this by identifying secondary and tertiary hyperalgesia (ie, increased pain sensitivity in undamaged tissue away from, and contralateral of the nociceptive source). Meaning that both bilateral cephalic and extracephalic PPTs were lower in people with CeH compared with healthy asymptomatic controls.^17^ However, these findings do not imply that peripheral nociceptive sources should be ignored. Such sources could initiate, maintain and modulate facilitated central pain processes. Therefore, potential nociceptive sources alongside psychological, behavioural and social components should also be assessed (ie, interplay of bottom-up and top-down mechanisms).^76^

Although CPM testing was already applied to people experiencing various types of headache such as chronic migraine, tension-type headache and post-traumatic headache,^18 77–79^ it was only once administered to people with chronic CeH.^75^ These people with chronic CeH experienced moderate pain (numeric pain rating scale 6.5±1.8) during CPM testing. We propose to analyse endogenous pain modulation during a headache-free phase. Having a less efficient CPM, when being headache free, suggests that on a pain-generating event, the person is at a higher risk to develop pain than people showing an efficient CPM at baseline.^29^

### The protocol

We propose a protocol to explore feasibility to assess PMPs in people with CeH. Interindividual variability in endogenous pain modulation is expected in these people due to their heterogeneous profile.^17 59 80 81^ Reduced endogenous pain modulation might be expected in people with CeH presenting with modifiable lifestyle and/or psychosocial risk factors for chronification. This hypothesis is supported by PPTs at the suboccipital muscles being influenced by the level of physical activity, stress, quality of life and screen time in people with CeH.^17^ Therefore, we will map the multidimensional PMP (ie, psychosocial lifestyle profile and pain profile) of each participant. Knowledge of a person’s profile might support an individual management programme as opposed to the traditional one-size-fits-all approach.^16^

We opted to use a dynamic protocol to assess the pain profile of people with CeH rather than relying exclusively on questionnaires and/or static measurements. Caution is indicated when screening questionnaires (eg, central sensitisation inventory) are used to identify human assumed central sensitisation. These questionnaires are not associated with widespread pain sensitivity and show a stronger association with psychological measures than with signs of facilitated central pain mechanisms.^82^

### Feasibility

Feasibility of the protocol is anticipated since it is designed according to the latest literature in the domain of TSP and CMP measurements.^24 51 52 55 65 68 69 83 84^ Collaboration with the AZ Vesalius hospitals (Tongeren and Bilzen, Belgium) is foreseen to obtain the required sample size of 12 people with CeH.^17 80 81^

A mitigation plan is composed to anticipate potential adverse events related to the testing procedure such as light headache, muscle soreness or sensitivity caused by mechanical pressure on cutaneous, muscular, nervous or arterial tissue. This plan includes general precautions such as informing participants on possible transient adverse effects, applying a strict protocol, using a wide cuff at the least uncomfortable test location (ie, calf muscles), and asking to abstain from vigorous physical activity at least 24 hours prior to the measurement. Potential adverse effects are expected to resolve within a 10 min recovery period.^85^ This feasibility study will provide useful information with regard to tolerability, planning, testing study procedures (eg, estimation of the recruitment rate, plausibility of multicentre collaborations) and investigating outcomes to support adequate sample size calculation.^73^ Furthermore, such study is designed to ensure that a possible future larger intervention study is achievable, rigorous and economically justifiable to avoid waste of resources.^73^ In the current context of a feasibility study, a data monitoring committee will not be involved. Adverse events are expected to be minor and transient in nature, and no long-term follow-up or interventions are applied.

Furthermore, measurements will be conducted with a respected interval (15 min after CPM) to limit carryover of the responses.^70 71^

### Limitations and suggestions

We acknowledge that assessing facilitated central pain mechanisms clinically is challenging for several reasons such as the absence of biomarkers to support its diagnosis. Although quantitative sensory testing is a promising surrogate measure to identify such facilitated mechanisms, it only evaluates evoked responses rather than spontaneous pain.^82^ Results should be interpreted within that context.

More research is needed into relevant modifiable psychosocial and lifestyle factors concerning sensitisation of pain in CeH.^86^ Sedentary time, anxiety, sleep quality, physical activity and stress were already reported to be associated with signs of central sensitisation in some people with CeH.^17^ Additionally, interindividual differences explain a large proportion of CPM variance.^87^ This finding forces researchers to look at the CeH population as more heterogeneous.^17 59^ We propose a feasibility study, which includes only 12 participants with CeH, which is the minimum recommended for pilot studies.^74^

Furthermore, WUR is reported to lack sensitivity to detect differences in the magnitude of sensitisation. Most studies report little variability (ratio 1.6–1.7) in WUR measures both in normal and hyperalgesic states. Therefore, we additionally propose to apply the SumSquare method as described by Allison *et al*.^54^ The potential future full-scale study should analyse endogenous pain modulation within a repeated-measures design to detect variance (ie, interindividual differences).^87^ Finally, using CPM, TSP and widespread hyperalgesia to compose the PMP can be time-consuming, expensive, and equipment is often not readily available in clinical practice. Therefore, the current protocol is an essential step towards further research (eg, assessing feasibility, validity, different populations), including development of easy-to-use alternative valid measurements to be widely implemented in clinical settings.
